#### 2.3.6. Pulmonary Function

Measurements will be taken in accordance with the guidelines of the European Respiratory Society and American Thoracic Society [38] and regarding the indications for the execution of respiratory function tests in the COVID-19 era [39]. During pulmonary function assessment, we will record the following parameters: VC (vital capacity), FVC (forced vital capacity), FEV_1_ (forced expiratory volume in 1 s), MEF_75_ (maximal expiratory flow at 75% of forced vital capacity), MEF_50_ (maximal expiratory flow at 50% of forced vital capacity), and MEF_25_ (maximal expiratory flow at 25% of forced vital capacity) using the portable Lungtest Handy (MES LLC, Cracow, Poland).

Further, the results of pulmonary parameters in the form of absolute values for FVC, VC, FEV_1_, MEF_25_, and data on race, sex, age, and height of the participant will be entered into the GLI 2012 (Global Lung Function Initiative, Berlin, Germany) calculator [40], yielding a percentage of the norm for healthy children. On this basis, the following parameters will be calculated: FEV_1_pred, FEV_1_%pred, FEV_1_%tile FEV_1_LLN, FEV_1_Z, VCpred, VC%pred, VC-LLN, VC Z, FEV_1_/VC, FEV_1_/VCpred, FEV_1_/VC%pred, FEV_1_/VC%tile, FEV_1_/VC-LLN, FEV_1_/VC Z, FVCpred, FVC%pred, FVC-LLN, FVC Z, FEV_1_/FVC, FEV_1_/FVCpred, FEV_1_/FVC%pred, FEV_1_/FVC%tile, FEV_1_/FVC-LLN, FEV_1_/FVC Z, MEF_25_pred, MEF_25_%pred, MEF_25_%tile, MEF_25_LLN, and MEF_25_ Z (where “pred” stands for predicted value, “%pred” for percentage of predicted value, “%tile” for percentile, LLN for lower limit of normal, and “Z” for Z score; the number of standard deviations the measured value differs from the predicted value).

### 2.4. Intervention Protocol

The water-based and land-based exercise training will be conducted twice a week, 45 min per session, for eight weeks. The exercises will be supervised by an experienced physiotherapist. 

Exercises in the water and on land will be matched in terms of intensity, duration, and muscle groups trained. Each session will consist of warm-up (8 min), aerobic training (32 min), and cool down (5 min). During the warm-up, participants will perform upper and lower limbs aerobics, breathing exercises, and stretches. The aerobic training component will consist of two circuit stations with endurance exercises for upper and lower limbs and a focus on breathing patterns. In each circuit, there will be five stations with different exercises. The activity at each station will last one minute, with 15 s rest periods in-between. At each station, the exercise will be performed by two participants together for motivation. The water-based and land-based exercises protocols are presented in Table 2. 

The aerobic training component will also include playing games (Table 3). The cool down will consist of upper-limb and thoracic cage stretches, and breathing control.

Participants will be encouraged to exercise at an intensity of 6–8 (“getting quite hard” to “hard”) on the Pictorial Children’s Effort Rating Table (PCERT) [29]. Training intensity will be measured twice during the aerobic exercise training, during each circuit. If participants report an exercise intensity below 6 on the PCERT, they will be encouraged to increase the intensity by increasing their speed and/or range of motion. After the first month of exercises, in order to make the classes more attractive and maintain exercise intensity, music and friendly competition between the participants will be introduced. Games will vary at each exercise session. Equipment used in the water-based exercise sessions will consist of floatation “noodles”, and that in the land-based exercise will consist of hand-held dumbbells, medicine balls, cones, and sashes. 

The land-based exercise sessions will be conducted in a gymnasium with a controlled temperature at the AWF Warsaw. The water-based exercise sessions will be conducted in a swimming pool (depth 1.2–1.5 m; length 12 m; width 3 m; water temperature approximately 30 °C; humidity 60%) at a fitness club in Warsaw, and participants will be encouraged to exercise at a depth where the water level sits between the clavicle and xiphisternum. 

The control (no exercise) group will be advised to not alter their current exercise routine and will be offered the option of joining a water-based or land-based exercise program after the final assessment has been completed.

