### 2.1. Study Population

Participants will be recruited from Warsaw’s primary schools and primary health-care units according to the inclusion criteria: (i) symptoms of post-COVID-19 condition lasting more than one month following initial COVID-19 infection confirmed by the diagnosis by general practitioner (including obligatory fatigue and shortness of breath/respiratory problems); (ii) age 10–12 years old. As it has been suggested that a positive COVID-19 test is not required for a diagnosis of post-COVID-19 condition [27], there will be an optional inclusion criteria: positive RT-PCR test and/or positive result in test for antibodies against the SARS-CoV-2 coronavirus 1–8 months prior to the study start. The exclusion criteria will consist of: absolute contraindications to exercise; unstable cardiac conditions; currently engaged in regular exercise training more than twice per week. The necessary minimum total number of participants (n = 84) was obtained using the G*Power program assuming detection of a moderate effect size of REPETITIONxGROUP interaction (d = 0.50 or eta square 0.06) for exercise capacity and fatigue with a significance level of 0.05 and statistical power of 0.85.

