### 2.2. Randomization

Participants meeting the inclusion criteria will be randomized to one of 3 groups: water-based exercise, land-based exercise, or control (no exercise). The randomization sequence will be designed by an investigator external to the study using an Excel random number generator. Group allocation will be prepared in 5 random versions. Finally, the allocation providing the lowest F value for MANOVA comparing basic characteristics of the study subjects will be used. Randomization will be stratified according to age, sex, and the level of exercise capacity. Concealed allocation will be achieved using opaque envelopes. Due to the nature of exercise interventions, it will not be possible to blind the physiotherapist or participants. 

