### 2.6. Statistical Analysis

Normality of the distributions of the quantitative variables under study will be tested using the Shapiro–Wilk test. Data will be presented as mean ± SD where appropriate. The mixed-design ANOVA will be used to compare means. The interaction of fixed and repeated factors will be analyzed. Tukey’s post hoc test will be used for detailed comparisons. For variables that do not meet the criteria of normality of distribution, data will be presented as medians and quartile range. The Mann–Whitney U test will be used to compare the groups. The variables as well as their increments will be analyzed. Effect sizes will be assessed by partial eta squared (ANOVA) or the Glass rank-biserial correlation coefficient (the Mann–Whitney U test). The agreement of children’s and parents’ responses in the PedsQLTM 4.0 questionnaire will be analyzed with the compatibility factor Kappa-k. All statistical calculations will be conducted using the Statistica 14.0.0.15 program (TIBCO Software Inc., Palo Alto, CA, USA, 2020).

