As this is the first study examining the effect of exercise training in children with post-COVID-19 condition, the frequency and duration of the exercise training program have also been modeled on existing evidence for exercise training in adults with chronic respiratory disease. It is unknown whether the intervention of twice weekly supervised group exercise training sessions for 8 weeks will be sufficient to induce physiological and psychological changes. In untrained healthy 12-year-old children, 8 weeks of endurance running was effective in inducing changes in VO_2_max and ventilatory threshold [53]. In adults with asthma, 12 weeks of aquatic exercises increased VO_2_max, but no improvements were demonstrated in pulmonary function [54]. However, in children, a 12-week aquatic or exergame play exercise program resulted in an increase in FVC [18]. 

The strength of the study described here is the simple design and low-cost exercise training intervention, which, aside from access to a pool or gym, requires no expensive equipment, making it feasible to implement. The interventions were designed according to four principles of effective interventions for children [55]: 1—optimize child’s engagement (through interesting equipment and creative activities); 2—provide a just-right challenge (selection of exercises and activities matching children’s skills and interests, and based on careful analysis of performance and behavior); 3—establish a therapeutic relationship (through therapist fostering a respectful, safe, and playful relationship emphasizing social group interactions); 4—provide adequate and appropriate intensity and reinforcement (rewarding system and dosage of intervention based on screening tests and age). Further, the intervention enables groups of patients to access therapy at the same time, which may have additional advantages for a child’s psychosocial wellbeing following many years of isolation due to lockdowns and periods of home schooling. 

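### Both exercise arms train in group sessions, but the named analyses and the n = 84 calculation treat every child as independent; if outcomes correlate within a class, error rates exceed the nominal level, most of all for water versus land

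*Protocol article*

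**What the plan says.** The Protocol article's section 2.2 randomises individual children to water-based exercise, land-based exercise or control. Section 2.4 describes twice-weekly supervised sessions for eight weeks in the two exercise arms. On the circuits it says "In each circuit, there will be five stations with different exercises" and "At each station, the exercise will be performed by two participants together for motivation". It also provides for games and, after the first month, friendly competition, and it calls the sessions classes. The Discussion presents group delivery as a strength ("the intervention enables groups of patients to access therapy at the same time") and lists social interaction in the group among the design principles. Controls keep their usual routine and attend no sessions until after the final assessment.

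On analysis, section 2.6 says "The mixed-design ANOVA will be used to compare means", followed by Tukey post hoc tests, with Mann-Whitney U for variables that are not normally distributed. No class or physiotherapist term is named. Section 2.1 obtains a minimum of 84 children for the group-by-time interaction "with a significance level of 0.05 and statistical power of 0.85", and mentions no design effect or ICC.

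**The concern.** This is a partially nested design: children in two arms share sessions, fellow participants and supervision, and children in the third do not. The ANOVA, Tukey and Mann-Whitney tests all take children within an arm as independent.

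If children in the same class tend to change together, an arm mean varies more than the analysis assumes. The understatement is larger for water versus land, where both means are affected, than for exercise versus control, where only one is. A class that happens to do well could then be read as an effect of water or of land exercise. Some correlation is plausible for self-reported fatigue, one of the two primary outcomes, because interaction in the group is an intended part of the intervention. It may be lower for exercise capacity, which is tested child by child on a treadmill.

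**Working it through.** **Inputs from the article.** Three arms; total 84, so 28 per arm if allocation is equal (the ratio is not stated); two measurements; alpha 0.05; power 0.85; effect size d = 0.50 or eta squared 0.06, that is f of about 0.25.

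**Assumptions, not in the article.** Class size c of about 10, inferred from 5 stations x 2 children; hence about three classes per exercise arm (10, 9 and 9). ICC of the change score from 0 to 0.10. Controls independent.

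**Step 1: the plan's own figure.** For the interaction, df1 = 2, df2 = N - 3 and lambda = f² x N x 2 / (1 - rho), where rho is the pre-post correlation. With f = 0.25, N = 84 and rho = 0.10, lambda = 0.0625 x 84 x 2 / 0.90 = 11.67 and power is 0.86. The figure of 84 is reached only for rho of about 0.06-0.10, which the article does not state, so it is consistent with the inputs but not determined by them. No variant that gives 84 includes a clustering allowance.

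**Step 2: loss of precision.** The design effect in each exercise arm is DE = 1 + (c - 1) x ICC. Relative to independence, the true standard error is larger by sqrt(DE) for water versus land and by sqrt((DE + 1) / 2) for exercise versus control. With c = 10:

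| ICC | DE | Water v land | Exercise v control |
|---|---|---|---|
| 0.01 | 1 + 9 x 0.01 = 1.09 | 1.04 | 1.02 |
| 0.02 | 1 + 9 x 0.02 = 1.18 | 1.09 | 1.04 |
| 0.05 | 1 + 9 x 0.05 = 1.45 | 1.20 | 1.11 |
| 0.10 | 1 + 9 x 0.10 = 1.90 | 1.38 | 1.20 |

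**Step 3: type I error of the planned tests.** Simulated under the null on change scores, 28 per arm, classes of about 10, nominal 5%. For two measurements, one-way ANOVA on change is the interaction test.

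| ICC | Omnibus test | Water v land, unadjusted | Exercise v control, unadjusted |
|---|---|---|---|
| 0 | about 5% | about 5% | about 5% |
| 0.01 | about 6% | about 6% | about 5.5% |
| 0.02 | about 7% | about 7% | about 6% |
| 0.05 | about 10% | about 10% | 7.5-8% |
| 0.10 | 14-15% | about 15% | about 10% |

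The Tukey familywise error is nearly the same as the omnibus error, so the planned post hoc procedure does not remove the problem.

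**Step 4: sensitivity to the class structure.** At ICC 0.05 and 0.10 the omnibus error is 8.2% and 11.7% with classes of 7, and 21.1% and 34.9% if each exercise arm is one class of 28. If dependence exists only within lasting pairs at the stations, it is 5.4% and 6.0%. Group sessions therefore matter far more than the pairing.

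**Step 5: what allowing for class costs.** The partially nested test takes the between-class mean square, pooled over the two exercise arms. With three classes per arm this has 2 x (3 - 1) = 4 df. For exercise versus control it is combined with the control variance, and the Satterthwaite df come to about 10-16. Size stays close to 5% for both comparisons. Power at a true ICC of 0:

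| Comparison | Effect | Unadjusted | Partially nested |
|---|---|---|---|
| Exercise v control | 0.5 SD | about 0.46 | 0.41-0.42 |
| Exercise v control | 0.8 SD | about 0.84 | 0.78-0.79 |
| Water v land | 0.5 SD | about 0.45 | 0.30 |
| Water v land | 0.8 SD | about 0.84 | 0.62 |

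**Step 6: the stated power.** With 84 children, f = 0.25 and rho = 0.10, approximate effective-sample power falls from 0.86 to 0.85, 0.80 and 0.75 at ICC 0.01, 0.05 and 0.10 if both exercise arms differ equally from control. If the effect lies between water and land, it falls to 0.83, 0.70 and 0.57.

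**The case against.** A reader might infer that the trial uses fixed classes and that its standard errors are therefore too small as a matter of fact. The documents support neither step. They describe group sessions but do not say that a child stays in one class, how many classes there are, or how large they are. Five stations with two children each is a statement about a circuit, from which class size is only inferred. No ICC is given; at 0.01 the inflation is slight, and movement between classes would weaken it further. The number of physiotherapists is also unclear: section 2.4 speaks of one, section 2.5 of several. If one person ran every class, there would be no instructor differences between classes within an arm. All of this stands, and it makes the size of the problem conditional.

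A reader might also infer that a class effect can be modelled at little cost throughout. That holds for exercise versus control only. For water versus land the class-level test has 4 df and loses 15-22 power points when there is no clustering. This objection stands too, and it argues against making the model primary.

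The last objection is that a condensed article may leave random effects to an analysis plan that is not shown. This carries less weight. Section 2.6 does more than stay silent: it names the model, the post hoc tests and the non-parametric alternative, and all of them assume an independence that the delivery in section 2.4 puts in doubt.

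**Conclusion.** The point holds in conditional form. The named analyses and the sample size treat children as independent although two of the three arms are delivered in groups. If outcomes correlate within class, the tests reject too often. With about 10 children per class, the omnibus error is about 6% at ICC 0.01 and rises to 14-15% at ICC 0.10, with water versus land the most exposed comparison.

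These sizes rest on an inferred class size, an assumed ICC range, equal allocation and stable class membership. Larger classes would make them worse; movement between classes would make them milder. The change is worth making before analysis because it is cheap. Confidence is medium, since the true ICC is unknown.

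**What to change.** 1. State the number and size of the classes in each exercise arm, and whether children stay in one class.
2. Record a class identifier and a physiotherapist identifier for each child in the water and land arms. Attendance is already recorded at every session.
3. Prespecify, as a required sensitivity analysis for exercise capacity and fatigue, a partially nested mixed model: a random class effect in the exercise arms only, its variance pooled over the two arms, with Satterthwaite or Kenward-Roger degrees of freedom. Report the ICC with it.
4. State that the 0.85 power assumes no class effect.
5. If each exercise arm turns out to be a single class, class and arm are confounded and no model can separate them. State this as a limitation.

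The cost is two data fields and one extra model, with no additional children. Intervals from the sensitivity analysis will be wider, considerably so for water versus land with only six classes. That is the reason to keep it as a sensitivity analysis and to read it alongside the primary result.

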### 2.5. Procedure

Participants will be recruited from Warsaw’s primary schools and primary healthcare units through various channels (flyers, e-mails, Facebook posts etc.) where information with a link and QR code to an online eligibility pre-screening questionnaire will be provided. The pre-screening will address the specific inclusion and exclusion criteria for the study, and basic demographic data. Concurrently, the eligible participants (children with parents) will be invited to undertake the main screening and diagnosis of a general practitioner at the Faculty of Rehabilitation, AWF Warsaw. The purpose of the study will be explained to the children and parents. After obtaining consent, the general practitioner will ensure all inclusion and no exclusion criteria have been met. Participants who meet the inclusion criteria will be invited to attend a baseline assessment at the Central Research Laboratory at AWF Warsaw. 

At the baseline assessment session, participants and parents will be requested to complete the PedsQL^TM^ 4.0 and CFSQ. The instructions will be explained by the principal researcher. In case of any doubt, parents and children will be able to ask the principal researcher for help. The research team will measure the participant’s weight and height and calculate body mass index (BMI). The general practitioner will perform an examination of the participants to determine any contraindications to exercise testing. Pulmonary function and exercise capacity testing will be performed. 

After completion of the baseline assessment, participants will be randomly assigned into one of three groups (water-based exercise, land-based exercise, or control), and simultaneous implementation of the two exercise programs will commence. The attendance rate will be recorded by the physiotherapists after each session. Children will also have attendance cards on which they will collect stamps to increase motivation to attend. After 8 weeks, all assessment measures for all participants will be repeated in the Central Research Laboratory at AWF Warsaw.

### 2.6. Statistical Analysis

Normality of the distributions of the quantitative variables under study will be tested using the Shapiro–Wilk test. Data will be presented as mean ± SD where appropriate. The mixed-design ANOVA will be used to compare means. The interaction of fixed and repeated factors will be analyzed. Tukey’s post hoc test will be used for detailed comparisons. For variables that do not meet the criteria of normality of distribution, data will be presented as medians and quartile range. The Mann–Whitney U test will be used to compare the groups. The variables as well as their increments will be analyzed. Effect sizes will be assessed by partial eta squared (ANOVA) or the Glass rank-biserial correlation coefficient (the Mann–Whitney U test). The agreement of children’s and parents’ responses in the PedsQLTM 4.0 questionnaire will be analyzed with the compatibility factor Kappa-k. All statistical calculations will be conducted using the Statistica 14.0.0.15 program (TIBCO Software Inc., Palo Alto, CA, USA, 2020).

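### The planned group-by-time test is valid but does not condition on baseline or the stratification factors, so it gives up precision that data already collected would supply

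*Protocol article*

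**What the plan says.** Section 2.3 (Outcome Measures) sets two assessments, one at baseline and one straight after the 8-week programme. Section 2.6 (Statistical Analysis) compares means with a mixed-design ANOVA. On the tested term it says "The interaction of fixed and repeated factors will be analyzed", and on follow-up tests "Tukey’s post hoc test will be used for detailed comparisons". It also analyses increments, uses the Mann–Whitney test for variables that are not normally distributed, and reports partial eta squared as the ANOVA effect size. It names no covariate.

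Section 2.1 (Study Population) powers the trial on the same term: a "moderate effect size of REPETITIONxGROUP interaction (d = 0.50 or eta square 0.06") at a "significance level of 0.05 and statistical power of 0.85", giving 84 children.

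Section 2.2 (Randomization) assigns children to three arms and states: "Randomization will be stratified according to age, sex, and the level of exercise capacity". It then uses whichever of five candidate allocations is best balanced on basic characteristics.

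**The concern.** The design takes trouble to balance the arms on age, sex and exercise capacity, but the stated model does not use those variables. If they predict the quantity being tested, the design has removed their contribution to differences between arms while the error term still carries it. Standard errors are then larger than they need be and the test leans conservative. Exercise capacity matters most here, because it is both a stratification factor and one of the two outcomes in the primary aim.

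Separately, testing change scores forces the follow-up value to move one-for-one with baseline. When the true slope is below 1, some removable noise stays in the comparison. With a minimum of 84 children over three arms and complete-case analysis, this loss of precision could decide whether a moderate benefit of either programme is detected.

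**Working it through.** **Inputs**
- Total N = 84 (section 2.1); three arms (section 2.2). The allocation ratio is not stated, so I assume equal arms: 84/3 = 28.
- Two time points (section 2.3).
- ρ, the correlation between an outcome's baseline and 8-week values, is not given. I use 0.3 to 0.9.
- SD² is assumed equal at both times and in all arms, with a common baseline slope.
- The target is a 0.50 SD between-arm difference at 8 weeks. This is my yardstick for a pairwise contrast and is not the omnibus effect in section 2.1.

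**Step 1: the plan's own figure.** For the interaction with 3 groups and 2 times, λ = f²·N·2/(1−ρ), with 2 and N−3 degrees of freedom and f = 0.25 for the stated d = 0.50.
- ρ = 0: λ = 0.0625×84×2/1 = 10.5, power 0.820; N for 0.85 power is 93.
- ρ = 0.1: λ = 10.5/0.9 = 11.67, power 0.861; N = 84.
- ρ = 0.5: λ = 10.5/0.5 = 21.0, power 0.986; N = 48.

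Using eta squared 0.06 instead (f = √(0.06/0.94) = 0.2526) gives N = 90, 81 and 48. So 84 is recovered with f = 0.25 and ρ = 0.1, a value the article does not state. The figure can be neither confirmed nor called wrong, and the rest does not depend on it.

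**Step 2: equivalence.** With two times, each child's within-subject contrast is the 8-week value minus baseline. The group-by-time F test is therefore the one-way ANOVA F test on that difference.

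**Step 3: variances.**
- Change score: 2(1−ρ)·SD²
- ANCOVA on baseline: (1−ρ²)·SD²
- Ratio: (1−ρ²)/[2(1−ρ)] = (1+ρ)/2

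For example, at ρ = 0.5 the variances are 1.00 and 0.75 SD², a ratio of 0.75. The equivalent N is 84 divided by the ratio.

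**Step 4: pairwise power with Tukey over three contrasts.** The critical |t| is 2.39 (studentized range for three means, about 81 df, divided by √2). The noncentrality is 0.50/√(2·variance/28). At ρ = 0.5 this is 0.50/√(2×1.00/28) = 1.87 for change scores and 0.50/√(2×0.75/28) = 2.16 for ANCOVA.

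| ρ (assumed) | Variance ratio | Change-score N matching 84 under ANCOVA | Power, change score | Power, ANCOVA |
|---|---|---|---|---|
| 0.3 | 0.65 | 129 | 0.22 | 0.34 |
| 0.5 | 0.75 | 112 | 0.31 | 0.41 |
| 0.7 | 0.85 | 99 | 0.51 | 0.59 |
| 0.8 | 0.90 | 93 | 0.71 | 0.77 |
| 0.9 | 0.95 | 88 | 0.96 | 0.97 |

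**Step 5: check on the three-group test.** In a simulation of 4,000 runs per setting, with 28 per arm and both exercise arms shifted by 0.5 SD, power of the change-score test versus ANCOVA was 0.35 vs 0.51, 0.47 vs 0.58, 0.68 vs 0.75 and 0.86 vs 0.89 at ρ = 0.3, 0.5, 0.7 and 0.8.

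These figures cover baseline adjustment only. Any further gain from age and sex cannot be quantified from the article.

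**The case against.** The strongest defence is that the planned test is sound. It is unbiased under randomisation, it is the term the sample size was built on, and preferring ANCOVA is a choice about efficiency. That stands, and it limits the point to lost precision. A separate analysis plan might add covariates; but the article does state its model, and powers the trial on the same unadjusted term.

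Several stronger readings are tempting but not supported:
- *Baseline is ignored.* It is not. It enters as the first repeated measure with its slope fixed at 1, and increments are analysed too. What is missing is conditioning on it.
- *Leaving out age and sex is costly.* Their stable effects cancel within each child, so they matter only if they predict change.
- *Tukey will be spread over all 15 pairs of the six group-by-time cells.* Section 2.6 does not say which means are compared, so this would be supposition.
- *The analysis cannot show which programme worked, because partial eta squared has no direction.* Reported means and Tukey comparisons supply direction.
- *ANCOVA can never be less precise.* That needs a common slope. In an illustrative simulation with slopes of 1, 1 and 0.3, a pooled-slope ANCOVA gave the contrast between the first two arms a variance of 0.0305, against 0.0260 for change scores.

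It also stands that the gain rests on an unstated correlation and becomes small when that is high.

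**Conclusion.** The point holds as one of efficiency and fit to the design. The stated main analysis is a valid, unadjusted change-score test that omits the factors used to stratify. Baseline adjustment would remove 35%, 25%, 15%, 10% or 5% of the variance of the arm comparisons at ρ = 0.3, 0.5, 0.7, 0.8 or 0.9. Under the same Tukey correction, this is worth about 12 percentage points of pairwise power at ρ = 0.3, 10 at 0.5, 8 at 0.7, 6 at 0.8 and 1 at 0.9. The figures assume equal arms of 28, equal variances, a common slope, no drop-out and a 0.50 SD difference. They do not show bias, an inflated false-positive rate or an error in n = 84. The change is worth making because the covariates are already being collected.

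**What to change.** In section 2.6, make the main analysis of each outcome an ANCOVA of the 8-week value on arm, the baseline value of that outcome, age, sex and baseline exercise capacity. When exercise capacity is itself the outcome, enter its baseline only once, since the baseline value and the stratification factor can be the same variable. Report the three between-arm adjusted mean differences with 95% confidence intervals, applying Tukey to those three contrasts.

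In section 2.1, add that n = 84 was derived for the unadjusted interaction.

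The cost is rewording these two sections. Baseline outcomes, age and sex are all obtained before allocation, so no extra visits, measurements or participants are needed.

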### Objectives

The primary aim of this research project is to determine the effectiveness of land-based and water-based exercise interventions on exercise capacity and fatigue in children with post-COVID-19 condition.

The secondary aims are to determine the effectiveness of land-based and water-based exercise on health-related quality of life and pulmonary function in children with post-COVID-19 condition, and to compare outcomes to norms for healthy children.

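### The plan does not make the between-arm difference in change the contrast that Tukey's test decides on, so it leaves open how each exercise programme will be judged against control

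*Protocol article*

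**What the plan says.** The primary aim (Objectives) is to "determine the effectiveness of land-based and water-based exercise interventions on exercise capacity and fatigue". Children are "randomized to one of 3 groups: water-based exercise, land-based exercise, or control (no exercise") and measured twice, at baseline and after the 8-week programme (section 2.3). The sample size of 84 in section 2.1 was obtained "assuming detection of a moderate effect size of REPETITIONxGROUP interaction".

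Section 2.6 then gives the analysis in this order:

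- A mixed-design ANOVA on the means, with its group-by-time interaction.
- Directly after that, the post hoc step: "Tukey’s post hoc test will be used for detailed comparisons".
- Where normality fails, medians and quartile range, with the Mann–Whitney U test for group comparisons.
- On change scores: "The variables as well as their increments will be analyzed".
- Effect sizes for both the ANOVA and the Mann–Whitney branch.

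The section does not name the means or contrasts to which Tukey's test is applied. It does not say which comparison decides that a programme works.

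**The concern.** With three arms and two time points the interaction has (3 − 1) × (2 − 1) = 2 degrees of freedom. It can show that the arms change differently, but not which arm differs from which. Any statement that water or land exercise beats control must come from the follow-up step.

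In the order of section 2.6, Tukey's test follows directly on the ANOVA means and their interaction, so the natural reading is pairwise comparison of the group-by-time means. None of those pairs tests the difference in change on which the trial is sized. Two things are at stake:

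- If within-arm pre-post pairs are used, recovery shared by all arms can be credited to a programme.
- If post-training pairs are used, a programme that works may be missed even though the interaction is significant.

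**Working it through.** **The plan's own figure.** For a within-between interaction with k = 3 arms and m = 2 times, the noncentrality is λ = f²·N·m/(1 − r), with 2 and N − 3 degrees of freedom. An eta squared of about 0.06 corresponds to f ≈ 0.25. At N = 84:

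- r = 0: λ = 0.0625 × 84 × 2 = 10.5, power 0.82.
- r = 0.1: λ = 10.5/0.9 = 11.7, power 0.86. The smallest N for power 0.85 is 82, or 84 with equal arms.

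So 84 is reached with r of about 0.1. The article does not state r, so the figure is neither confirmed nor refuted. The point below does not depend on it.

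**What Tukey's test compares.** Three arms by two times give 6 means and 6 × 5/2 = 15 pairs:

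- 3 pre-post pairs within an arm
- 3 between-arm pairs at baseline
- 3 between-arm pairs after training
- 6 pairs that mix arm and time

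None is (change in a programme) − (change in control). With two time points, however, the interaction F is identical to the F of a one-way ANOVA on the increments. Tukey's test on those increments gives exactly the pairwise differences in change.

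**Power for one programme against control.** Assumptions: 84/3 = 28 per arm (equal allocation is not stated), SD 1 at both times, a 0.5 SD gain in both exercise arms and none in control, α = 0.05. The document gives no value for r, so it is varied. A pair is declared different when the observed difference exceeds q·√(s²/n). The standard error of the difference is √(2s²/n).

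- Post-training pair, six means: s² = 1, q ≈ 4.08. Threshold 4.08 × √(1/28) = 0.771; standard error √(2/28) = 0.267. z = (0.5 − 0.771)/0.267 = −1.01, so power is about 16% whatever r is.
- Increments, three means: s² = 2(1 − r), q ≈ 3.38.

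| r | s² | Threshold | Standard error | z | Power, increments (simulated) | Power, post-training pair |
|---|---|---|---|---|---|---|
| 0.1 | 1.8 | 0.857 | 0.359 | −1.00 | 16% | 16% |
| 0.3 | 1.4 | 0.756 | 0.316 | −0.81 | 21% | 16% |
| 0.5 | 1.0 | 0.639 | 0.267 | −0.52 | 31% | 16% |
| 0.7 | 0.6 | 0.495 | 0.207 | 0.03 | 52% | 16% |
| 0.8 | 0.4 | 0.404 | 0.169 | 0.57 | 71% | 16% |

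The z values agree with the simulated powers to within about a percentage point. With a 0.8 SD gain, the increments give 73% (r = 0.5) and 93% (r = 0.7), against 55% and 54% for the post-training pair. Both contrasts estimate the same effect: the mean estimates were about 0.50 and 0.80.

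**Reading the pre-post pairs.** Assume that water has no effect, land adds 0.5 SD, and all arms recover by 0.5 SD.

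- Water's pre-post pair is significant together with the interaction in 13%, 42% and 76% of trials at r = 0.5, 0.7 and 0.8. Control's pre-post pair is significant about as often as water's.
- The pattern that would mislead is a significant interaction, a significant pre-post change in water and none in control. It occurs in about 3–17% of trials over r = 0.1–0.8 (11%, 17% and 9% at r = 0.5, 0.7 and 0.8).
- Tukey's test on the increments declares water different from control in about 2%.

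If no programme works and all arms recover by 0.5 SD, a given exercise arm is significant pre-post and control is not in 23% (r = 0.5) and 21% (r = 0.7) of trials. When a significant interaction is also required, this falls to about 1.5%.

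**The case against.** A reader might infer that the plan never tests a difference in change and so cannot say which programme beat control. The documents do not support this, for two reasons.

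- Section 2.6 says that increments will be analysed. The sentence follows the Mann–Whitney test, but the next one covers effect sizes for both branches, so a general reading is possible. On that reading the plan already contains the right ingredients.
- The arms are randomised, so a post-training comparison with control is a valid test of the programme. Its weakness is power, not bias.

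The size of the loss also depends on r. There is none at r = 0.1, which is about the value that reproduces the sample size of 84. At r = 0.5 the two standard errors are equal, and the whole gap comes from adjusting for six means rather than three.

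Nor is the 76% figure the risk of a false claim. In most of those trials control also improves significantly, which a careful reader would notice. The plan nowhere says that a within-arm change proves effectiveness.

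Finally, a statistical analysis plan that is not shown could name the contrasts.

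These arguments limit the point but do not remove it. The article chose to specify the post hoc method and placed it where its natural reading does not match the hypothesis the trial is sized on. Even on the generous reading, levels and increments are both analysed and nothing says which one decides.

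**Conclusion.** The point holds in a limited form. Section 2.6 does not make the between-arm difference in change the deciding contrast, and the branch to which the increments sentence belongs is unclear. If Tukey's test is run on the six means, the pairs offered are either within-arm changes, which cannot separate a programme's effect from common recovery, or post-training differences, which are unbiased but weaker at moderate or high r.

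Under the stated assumptions the power given up for a 0.5 SD gain is 0, 5, 15, 36 and 55 percentage points at r = 0.1, 0.3, 0.5, 0.7 and 0.8. The misleading pre-post pattern arises in about 3–17% of trials, against about 2% for the change contrast.

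These sizes rest on 28 per arm, equal SDs, normal data and assumed values for r, the gains and the recovery. The document gives none of the last three for this calculation; the 0.5 SD gain is illustrative. The change should be made because it removes an ambiguity in the primary conclusion at almost no cost. The trial is not shown to be invalid.

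**What to change.** Replace the Tukey sentence in section 2.6 with:

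> Following the REPETITIONxGROUP test, the three between-arm differences in change (water−control, land−control, water−land) will be estimated with 95% confidence intervals, Tukey-adjusted for three comparisons (Tukey after one-way ANOVA on the increments). Effectiveness will be concluded only from the difference in change versus control; within-arm pre-post changes are descriptive.

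This also settles that the increments belong to the ANOVA branch. It changes wording only and needs no further data, participants or software. The small downside is that within-arm p-values can no longer support an effectiveness claim.
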